**1. Study Subjects**

Recruit 60 stroke patients hospitalized in the Department of Rehabilitation Medicine, Yancheng First People's Hospital.

**1.1 Inclusion Criteria**

(1) Stroke diagnosed by CT or MRI.

(2) Age 40-80 years old.

(3) Stable condition, first onset of illness, duration 1-3 months.

(4) Able to walk independently or with assistance for more than 10m, Brunnstrom stage III-V lower limb.

(5) Cognitive clarity, ability to follow simple verbal commands or instructions, MoCA≥26.

(6) Informed consent signed by the patient or his/her relatives.

(7) No history of epilepsy.

(8) No contraindications to TMS examination.

**1.2 Exclusion Criteria**

(1) Individuals with relevant contraindications to TMS (pacemakers, intracranial implants, implanted drug pumps etc.).

(2) Significant speech, attention, auditory, visual (lateral neglect, hemianopsia, etc.), intellectual, psychiatric or cognitive dysfunction.

(3) Prior history of organic brain disease, neuropsychiatric history, drug abuse and alcoholism. (4) Patients with severe failure of vital organs (e.g., heart, lung, liver, kidney).

(5) Patients with pre-existing lower limb motor dysfunction prior to the stroke.

(6) Those who are currently participating in other clinical trials.

(7) Those who cannot co-operate with the functional assessment and have poor compliance. (8) Inability to induce a TMS response in the tibialis anterior muscle prior to formal testing.

(9) Pregnancy.

(10) Use of drugs that affect cortical excitability (e.g., benzodiazepines, baclofen, antiepileptics, certain antidepressants) that cannot be safely tapered or washed out prior to study participation.

**2. Sample Size Estimation**

Assuming the endpoint FMA-LE scale value in the preconditioned iTBS group is 3 points higher than in the non-preconditioned iTBS group, and the combined standard deviation for all groups is 2.5 points. Based on existing research results and clinical experience, at a statistical significance level of α=0.05, to achieve 90% statistical power, and considering a 20% follow-up loss rate, calculation using PASS 15 software indicates: at least 20 patients are needed per group, totaling 60 patients.

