**3. Random Grouping**

A total of 60 eligible stroke patients will be enrolled in this study. Following the baseline assessment, a computer-generated randomization sequence will be used to assign all participants in a 1:1:1 ratio to one of three parallel intervention groups: the priming iTBS group (n=20), the non-priming iTBS group (n=20), or the sham stimulation group (n=20). The allocation sequence will be concealed from the researchers enrolling participants. After a participant provides informed consent and all baseline assessments (T0) are completed, the research coordinator will access the central web-based system. The system will then reveal the group allocation only to the unblinded physical therapist responsible for administering the intervention. This ensures that outcome assessors and participants remain blinded.

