**6. Statistical Analysis**

SPSS 22.0 software will be used. Demographic and baseline characteristics will be compared using one-way analysis of variance (ANOVA) or Fisher's exact test. Mixed-design ANOVA (between-subjects factor: group; within-subjects factor: time) and the interaction between time and group will be analyzed to compare dependent outcomes across groups at the three time points (T0-T0, T1-T0, and T2-T0). The significance level is set at P < 0.05. If any significant time-by-group interaction effects are found, pairwise t-tests will be used for comparisons, comparing baseline changes with a Bonferroni correction threshold of 0.017. If any significant time-by-group interaction effects are found, exploratory subgroup analyses will be conducted to investigate potential differential effects among different functional groups. Due to the exploratory nature of the study, we applied the Bonferroni correction only in the post-hoc comparisons of the primary outcome (P=0.017, number of comparisons=3).

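### The 90% power is set at α=0.05, but the priming vs non-priming comparison it describes is judged at 0.017; after the planned losses that gives about 80%

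*Protocol*

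**What the plan says.** Protocol section 2 (Sample Size Estimation) assumes that "the endpoint FMA-LE scale value in the preconditioned iTBS group is 3 points higher than in the non-preconditioned iTBS group" and that "the combined standard deviation for all groups is 2.5 points". The other inputs are given as "at a statistical significance level of α=0.05, to achieve 90% statistical power, and considering a 20% follow-up loss rate", and the result is that "at least 20 patients are needed per group, totaling 60 patients". The section does not name the test, its sidedness or any expected sham mean, and it does not mention a multiplicity correction. Section 3 randomises 1:1:1 to three groups, and section 5.1 makes FMA-LE the primary outcome.

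Section 6 (Statistical Analysis) first tests the group-by-time interaction in a mixed-design ANOVA at 0.05. If that is significant, pairwise t-tests follow, "comparing baseline changes with a Bonferroni correction threshold of 0.017". The section closes by saying that the correction covers only the primary outcome's post-hoc comparisons, and that there are three of them.

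**The concern.** The one contrast named in the sample-size statement is a pairwise contrast on the primary outcome. Section 6 tests such contrasts at about a third of the significance level used to size the trial. A stricter threshold at the same sample size lowers power, so 90% cannot hold for that comparison on the same inputs.

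What is at stake is how a non-significant result is read. Someone relying on section 2 would put the chance of missing a true 3-point advantage of priming at about 10%. Under the test as planned, and at the loss rate the protocol itself expects, it is about 20%. Type I error is not affected.

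**Working it through.** **Inputs (section 2 unless noted).** Difference 3 points; SD 2.5; α 0.05; power 90%; loss 20%; 20 per group; pairwise threshold 0.017 (section 6). Two assumptions are mine: tests are two-sided, and (until step 4) 2.5 is the SD of whatever quantity is tested.

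**1. Reproduce the plan's figure.** Standardised difference d = 3/2.5 = 1.2. Power of a two-sample t-test with n per group comes from the noncentral t distribution with 2n − 2 degrees of freedom and noncentrality d·√(n/2).

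- n = 15, two-sided 0.05: 88.7%.
- n = 16, two-sided 0.05: 90.7%.

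So 16 evaluable per group are needed, and 16/(1 − 0.20) = 20 enrolled per group, 60 in total. This matches exactly. A one-sided 0.05 test needs 13 evaluable, hence 13/0.8 = 16.25, or 17 enrolled, which does not match.

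**2. Same inputs at the section 6 threshold.** For n = 16 the noncentrality is 1.2·√8 = 3.394 on 30 degrees of freedom. The critical value rises from 2.042 (at 0.05) to 2.527 (at 0.017).

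| Evaluable per group | Power at 0.05 | Power at 0.017 |
|---|---|---|
| 16 (after 20% loss) | 90.7% | 80.1% |
| 20 (no loss) | 95.9% | 89.7% |
| 21 | 96.7% | 91.3% |

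The type II error with 16 per group goes from 9.3% to 19.9%. Other ways of computing the 0.017 figure with 16 per group give 79.9% (threshold exactly 0.05/3), 81.6% (error variance pooled over three groups) and 84.3% (normal approximation).

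**3. Add the interaction gate.** I approximated it by a one-way F test at 0.05 across the three groups at a single time point, by simulation. Requiring both that F test and a pairwise p below 0.017, with 16 per group, gives about 79–80% whether the sham mean is equal to, 1.5 points above or 3 points below the non-priming mean. The gate costs little here because the 0.017 threshold is already the stricter hurdle.

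**4. Which SD?** Section 2 speaks of the endpoint value; section 6 tests change from baseline. If 2.5 is the endpoint SD, baseline variance is equal and the baseline–endpoint correlation is r, then the change-score SD is 2.5·√(2(1 − r)). No value of r is given, so a range is needed:

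| r | SD of change | d | Power at 0.017, 16 per group |
|---|---|---|---|
| 0.4 | 2.74 | 1.10 | 71% |
| 0.5 | 2.50 | 1.20 | 80% |
| 0.6 | 2.24 | 1.34 | 89% |
| 0.7 | 1.94 | 1.55 | 96% |

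**5. Would 0.05 for this comparison restore 90%?** Only without the gate. With 16 per group and SD 2.5, a pairwise test at 0.05 that must also pass the F test has about 84% power if the sham mean lies midway between the two iTBS means, about 89% if sham equals non-priming, and about 91% if sham is 3 points below non-priming. Without the gate it is 90.7%.

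**The case against.** Section 2 names no test, and its SD for all groups combined would also suit a three-group F test. If the sham mean is taken as 0.3 to 0.4 points above non-priming, a one-way F test at 0.05 also needs 16 evaluable per group (power 90.9% and 90.1%), hence 20 enrolled. On that reading α=0.05 would match the level at which section 6 tests the interaction, and 0.017 would govern only what follows. This stands to the extent that the t-test is the likeliest derivation and not the only one. It is the less natural reading, because an F-test calculation needs a sham mean and section 2 gives none. Even so, the claim that priming beats non-priming would still rest on the 0.017 test.

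Section 6 also does not say which three comparisons it counts. The three group pairs are the natural reading with three arms, and 0.017 applies to the primary-outcome pairwise tests in any case.

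The study describes itself as exploratory, but it says so to confine the correction to the primary outcome, which is where the power is claimed.

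Three stronger readings may tempt a reader, and the document does not support them:

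- **That 60 patients give only 80%.** The 80% belongs to 48 evaluable patients after the full planned loss; 60 retained give 89.7%.
- **That about 80% is a firm figure.** It depends on an SD for change that the protocol does not state, and with a baseline correlation of 0.7 the shortfall disappears.
- **That the trial is too small and must grow.** Reaching 90% at 0.017 would take 21 evaluable per group (21/0.8 = 26.25, so 27 enrolled, 81 in total), but about 80% is not a failed design. The fault is in the statement of power.

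**Conclusion.** The inconsistency is real and should be fixed. Section 2 claims 90% at 0.05 for a comparison that section 6 decides at 0.017, so the stated power is not a property of the planned pairwise test. With 2.5 as the SD of the change score and two-sided tests, the planned 20% loss leaves about 80% power, roughly doubling the chance of missing the assumed effect; with no losses the gap is negligible. If 2.5 is the endpoint SD, the figure could lie either side of 90%, and the protocol does not allow a choice. No patient or procedure is affected, so this is a correction that should be made, not one that invalidates the design.

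**What to change.** **Preferred.** Restate section 2 to give about 80% power at two-sided 0.017 with 16 evaluable per group, and 89.7% with no losses. Name the test, and say whether 2.5 is the SD of the endpoint or of the change from baseline. If it is the endpoint SD, state the assumed baseline correlation and recompute. Section 6 should list the three comparisons. The cost is a less favourable stated power.

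**Alternative, if the sponsor prefers it.** Pre-specify priming versus non-priming iTBS on FMA-LE, at a stated time point, as the single primary comparison at two-sided 0.05, and say explicitly that it does not depend on the interaction test. The comparisons with sham then follow in a fixed order or become secondary. N=60 supports the stated 90% only with the gate removed for this comparison, and only if 2.5 is the SD of the quantity tested. The cost is lower status for the sham comparisons, which is a design choice for the sponsor.

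Both routes change only the wording of sections 2 and 6 and need no extra patients. The change should be made before any unblinded data are seen.

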**3. Random Grouping**

A total of 60 eligible stroke patients will be enrolled in this study. Following the baseline assessment, a computer-generated randomization sequence will be used to assign all participants in a 1:1:1 ratio to one of three parallel intervention groups: the priming iTBS group (n=20), the non-priming iTBS group (n=20), or the sham stimulation group (n=20). The allocation sequence will be concealed from the researchers enrolling participants. After a participant provides informed consent and all baseline assessments (T0) are completed, the research coordinator will access the central web-based system. The system will then reveal the group allocation only to the unblinded physical therapist responsible for administering the intervention. This ensures that outcome assessors and participants remain blinded.

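### Neither the described randomisation nor the stated FMA-LE model accounts for time since stroke onset across a 1-3 month entry window, which may cost precision but does not bias the trial

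*Protocol*

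**What the plan says.** - **Entry window.** Protocol section 1.1 requires "Stable condition, first onset of illness, duration 1-3 months". The same list also sets a range of severity: "Able to walk independently or with assistance for more than 10m, Brunnstrom stage III-V lower limb".
- **Allocation.** Section 3 states that "a computer-generated randomization sequence will be used to assign all participants in a 1:1:1 ratio", with 20 patients per arm and concealment through a central web-based system. It names no stratification factor, blocks or minimisation.
- **Analysis.** Section 6 gives a mixed-design ANOVA ("between-subjects factor: group; within-subjects factor: time") on changes from T0, then pairwise t-tests at 0.017. Baseline characteristics are compared by significance tests, but nothing follows from the result. No covariate is named.
- **Planning values.** Section 2 assumes that "the endpoint FMA-LE scale value in the preconditioned iTBS group is 3 points higher than in the non-preconditioned iTBS group" and that "the combined standard deviation for all groups is 2.5 points", "at a statistical significance level of α=0.05, to achieve 90% statistical power", with 20% loss to follow-up.

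**The concern.** The latest entrant may be three times as far from the stroke as the earliest, and the primary outcome is judged on change over a 4-week course. If patients who enter early tend to gain more (or less) whatever stimulation they receive, onset time is a prognostic factor for that change.

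Two things then follow. The spread it causes stays in the error term when the model contains only group and time. And with 20 patients per arm, two arms can differ noticeably in their mix of early and late entrants, so that anyone reading an observed difference must wonder how much of it reflects that mix.

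The stakes are precision and interpretability. The factor is already recorded, because eligibility depends on it.

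**Working it through.** **1. The plan's own figure.** Inputs from section 2: difference 3, SD 2.5, alpha 0.05 (taken as two-sided, since the sidedness is not stated), power 90%, loss 20%.
- Normal formula: 2 × (1.960 + 1.282)² × 2.5² / 3² = 14.6, so 15 per arm, and 15 / 0.8 gives 19.
- Exact t calculation: 16 per arm (power 90.7%), and 16 / 0.8 = 20. This matches the stated 20.

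**2. Starting power.** With 16 completers per arm and the section 6 threshold of 0.017, the exact t calculation gives 80%. This applies the SD of 2.5 to the change score, which is an assumption.

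**3. How unequal the arms can be.** Assume entry times uniform over 30 to 90 days, so SD = 60 / √12 = 17.3 days.

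| Per arm | SE of difference in mean onset, 17.3 × √(2/n) | 95% range | Differ by more than 7 days | More than 14 days |
|---|---|---|---|---|
| 20 | 5.5 days | ±10.7 | 20% | 1.1% |
| 16 | 6.1 days | ±12.0 | 25% | 2.2% |

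Put as the share entering before 2 months, two given arms of 20 differ by 20 percentage points or more in about 27% of simulated trials. Some pair of the three arms does so in about 51%.

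**4. What that means in FMA-LE points.** Let r be the correlation of onset time with FMA-LE change. The documents give no value, so a range is shown. The 95% range of the chance shift with 20 per arm is ±1.96 × r × 2.5 × √(2/20):
- r = 0.2: ±0.31 points
- r = 0.3: ±0.46 points
- r = 0.5: ±0.77 points

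For comparison, the target is 3 points and the contrast's own SE is 2.5 × √(2/20) = 0.79.

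Alternatively, assume that early entrants gain 2 points more than late ones. A 20-point imbalance then shifts the contrast by 0.20 × 2 = 0.4 points. With half the patients in each class, the gap accounts for (2²/4) / 2.5² = 1.0 / 6.25 = 16% of the planned variance.

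**5. What adjustment gains** (16 per arm, alpha 0.017). Residual SD is 2.5 × √(1 − r²), or √(6.25 − 1.0) for the 2-point gap.

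| Assumed link | Residual SD | Power |
|---|---|---|
| none | 2.50 | 80% |
| r = 0.2 | 2.45 | 82% |
| r = 0.3 | 2.38 | 84% |
| 2-point gap | 2.29 | 87% |
| r = 0.5 | 2.17 | 91% |

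**6. Error rates without adjustment.** In simulated trials with no treatment effect, the false-positive rate was 4.8-5.2% at 0.05 and 1.7-1.8% at 0.017, for r from 0 to 0.7. The overall rate is therefore nominal.

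Within imbalanced trials it is higher. With 16 per arm, about 21% of trials have an early-share difference of 20 points or more. For a 2-point gap, the rate at 0.017 in those trials is about 3.5%. The remaining 79% compensate: (1.7 − 0.21 × 3.5) / 0.79 = 1.2%.

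**The case against.** A reader might infer that chance imbalance in natural recovery can pass for a treatment effect, so that the trial is biased or prone to false positives. The documents do not support that. Allocation is random and concealed, and imbalance in a prognostic factor is part of the sampling error that the test already allows for. Step 6 shows nominal overall error rates. This objection stands in full.

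Other objections:
- **Recovery is not described.** Nothing in the protocol says that spontaneous recovery slows, sharply or otherwise, between month 1 and month 3. This stands: the link between onset time and change is an assumption, and every gain above depends on it.
- **Large gaps are hard to credit.** A 4-point early/late gap would imply (4²/4) / 6.25 = 64% of the planned variance. This stands, and the illustration stops well short of it.
- **The SD of 2.5 may already include onset-related variation.** It may. The unadjusted calculation is then not undermined, and adjustment is a gain on top of it. Step 5 takes that reading.
- **Silence is not exclusion.** Section 3 does not say that randomisation is unstratified, and covariates may be left to a statistical analysis plan. This stands in part. But section 6 names its model without a covariate, and an analysis plan cannot stratify an allocation after the fact.
- **Other factors could be chosen.** Brunnstrom stage or baseline FMA-LE could also serve. This is true, and it does not count against using onset time.

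**Conclusion.** The point holds as a matter of efficiency and interpretability. The entry window is wide, and time since onset appears in neither the described allocation nor the stated model. Whether this matters depends on a prognostic link that the protocol does not quantify. If that link is weak (r = 0.2 to 0.3), power rises from 80% to 82-84%; if moderate (a 2-point gap, or r = 0.5), to 87-91%. If there is no link, almost nothing is lost by adjusting.

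The likely chance shift is well below the 3-point target. The rise in error rate is confined to trials that happen to be imbalanced and is offset in the others. The stated 20 per arm does not change on this account.

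These figures assume uniform entry over the window, an SD of 2.5 for change, a two-sided test and 16 completers per arm.

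**What to change.** **Section 6 (main change).** Prespecify days since onset, as a continuous covariate, in the model for FMA-LE. Because the question concerns change over time, let the covariate interact with time; a main effect alone would leave the group-by-time comparison as it is. Take the three pairwise comparisons as adjusted contrasts, since raw t-tests on change would drop the covariate again.

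**Section 3 (optional).** Have the central web-based system stratify on time since onset at a fixed cut within the 1-3 month window, using permuted blocks, and include that stratum in the model. The documents give no basis for a particular cut, so the choice should be stated and fixed before enrolment. The covariate alone gives most of the benefit.

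**Cost.** No new data are needed, because onset time is already required for eligibility. The analysis spends one or two degrees of freedom. If stratified, incomplete blocks may leave arm sizes off 20/20/20 by one or two patients.

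### Allocation names no severity stratification factor and the stated model no severity covariate, although eligibility spans Brunnstrom III to V; stratifying on one baseline factor would be a cheap gain in balance and precision

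*Protocol*

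**What the plan says.** **Eligibility.** Protocol section 1.1, criterion (4): "Able to walk independently or with assistance for more than 10m, Brunnstrom stage III-V lower limb". That is three lower-limb recovery stages and two levels of walking ability.

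**Allocation.** Section 3: "a computer-generated randomization sequence will be used to assign all participants in a 1:1:1 ratio to one of three parallel intervention groups". It also describes concealment, a central web-based system consulted after consent and all T0 assessments, and who learns the arm. It names no stratification or minimisation factor.

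**Planning figures.** Section 2 plans on a 3-point advantage in FMA-LE for priming over non-priming iTBS. For the spread it assumes that "the combined standard deviation for all groups is 2.5 points". The result is that "at least 20 patients are needed per group, totaling 60 patients".

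**Analysis.** Section 6 compares changes from T0 in a mixed-design ANOVA with group and time as its factors. If the time-by-group interaction is significant, "exploratory subgroup analyses will be conducted to investigate potential differential effects among different functional groups". Those functional groups are not defined.

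**The concern.** Section 5.1 describes FMA-LE as a measure of lower-limb motor impairment and recovery that includes synergistic movement. Lower-limb Brunnstrom stage grades much the same thing, so the eligibility range spreads patients along the primary outcome itself. With 20 per arm and no balancing on severity, one arm can by chance hold noticeably more stage III patients than another. Neither the stated allocation nor the stated model deals with that.

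Three things are at stake: the balance of the arms on an obvious prognostic factor, the precision of the FMA-LE comparison, and the make-up of the functional subgroups. The timing also matters. A covariate can still be specified in an analysis plan, but a stratified allocation has to be set before the first patient is randomised.

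**Working it through.** **1. The plan's own sample size.** Inputs from section 2: difference 3, SD 2.5, "at a statistical significance level of α=0.05, to achieve 90% statistical power", "considering a 20% follow-up loss rate". Sidedness is not stated; two-sided is assumed. The standardised difference is 3/2.5 = 1.2. A two-sample t-test needs 15.6, so 16, per arm, and 16/0.8 = 20. The stated 20 per group reproduces, with power 0.907 at 16 per arm.

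**2. Chance imbalance at the plan's own SD.** Assume that 2.5 also describes FMA-LE at T0. For two arms of 20:
- SE of the difference in means = 2.5 × √(2/20) = 0.79.
- 95% limits = ±1.96 × 0.79 = ±1.55 points, about half the target.
- P(gap ≥ 1 point): 1/0.79 = 1.26, two-sided probability about 21%.
- P(gap ≥ 3 points): about 0.015%.
- The 95% limit reaches 3 points only if the SD is 3/(1.96 × √0.1) = 4.84, nearly twice the stated value.

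**3. Imbalance from stage alone.** Assumptions, not in the documents: 20 patients in each of stages III, IV and V; arms of exactly 20; adjacent stage means g points apart. Score the stages −1, 0, +1. The gap between two arms is g times the difference in mean score, which has standard deviation √[(40/59) × (2/20)] = 0.260. Enumerating every possible allocation gives, for two given arms:

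| g (points) | SD of gap | P(gap ≥ 1) | P(gap ≥ 3) |
|---|---|---|---|
| 3 | 0.78 | 21% | 0.01% |
| 4 | 1.04 | 39% | 0.5% |
| 5 | 1.30 | 50% | 2.6% |

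Two given arms differ by 4 or more stage III patients in about 24% of trials.

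One caution applies to the lower rows. With equal thirds, stage differences alone contribute an SD of g × √(2/3): 2.45, 3.27 and 4.08 for g = 3, 4 and 5. The last two exceed the 2.5 in section 2, so those rows assume a more varied population than the plan does.

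**4. What the change score leaves.** A level difference present equally at T0 and T2 cancels in T2−T0. If the T0–T2 correlation is ρ and the SDs are equal, a baseline imbalance d leaves (ρ − 1) × d in the change. For d = 1.55 that is 0.78, 0.47 and 0.16 points in size at assumed ρ of 0.5, 0.7 and 0.9.

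**5. Subgroups.** Three stages in an arm of 20 give 20/3 = 6.7 patients per cell. Under the assumptions of step 3, at least one of the nine cells has 3 or fewer patients in about 22% of trials. If patients are instead drawn at random from a population with equal stage shares, the figure is 45%. Even with perfect balance, 7 per arm gives about 54% power for 3 points at SD 2.5 and α = 0.05.

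**The case against.** The strongest objection is that section 6 analyses change from T0. The step 3 gaps are differences in level, and a stable level difference drops out. This stands, and it removes most of the apparent threat. Only a link between severity and the amount of recovery survives, including any ceiling effect on a 34-point scale. The documents do not quantify that link.

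Unstratified randomisation is also valid: chance imbalance is already allowed for in the type I error rate. Section 3 is silent about restriction rather than excluding it, and its fixed 20 per arm suggests some blocking. Both points stand. The calculation already fixes the arms at 20, and blocking without a severity factor would not be expected to balance stage.

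The subgroup argument is limited too. Those analyses are exploratory and conditional, equating functional groups with Brunnstrom stage is an inference, and stratification would not make cells of about 7 informative. Covariates and subgroup definitions may also sit in an analysis plan that is not shown. The stratification factor is different, because it belongs to the allocation and cannot be added afterwards.

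A reader might infer two stronger things. The first is that chance imbalance could equal the 3-point target; steps 2 and 3 do not support this. The second is that the wide eligibility leaves the trial well short of 90% power. That would need stage-specific SDs which the documents do not give and an unadjusted endpoint test which section 6 does not plan. Whether 2.5 is a sound SD, and whether it refers to an endpoint value or a change, is a separate sample-size question.

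**Conclusion.** The point holds as a cheap improvement in balance and precision; it is not an error of validity. The protocol names no severity factor in its allocation and no severity covariate in its stated model. A chance gap of at least 1 point between two given arms, a third of the target, has probability about 21% at the plan's own SD. From stage imbalance alone it is 21% to 50%, if stages are equally represented and adjacent stages differ by 3 to 5 points. A 3-point gap stays under 3% throughout. After the planned change from T0, a 1.55-point imbalance leaves about 0.2 to 0.8 points over assumed correlations of 0.9 down to 0.5. The stated sample size reproduces and is not disputed here.

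**What to change.** - **Section 3:** stratify the web-based randomisation by one severity factor known at T0, for example Brunnstrom III versus IV-V, using small permuted blocks in multiples of three, with block sizes concealed. With equal thirds, this split accounts for 0.5 of the 0.667 stage-score variance, that is 75%. It does not balance IV against V.
- **Section 6:** include the stratification factor and baseline FMA-LE in the primary model. Baseline FMA-LE should take up much of what the two-level factor leaves. Use the same factor to define the functional groups, and keep those analyses exploratory.

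**Cost:** one setting in a system already planned and a sentence in each of sections 3 and 6. No extra patients, visits or measurements are needed. With 60 patients and two strata some blocks will be incomplete, so arms may not be exactly 20 each, and allocation becomes slightly more predictable if block sizes become known. If recruitment has already started without stratification, the model adjustment alone still recovers most of the benefit.
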